### Study design and setting

The study is a single-centre, observational, prospective cohort of all consecutive individuals with an acute STEMI diagnosis presenting to the CMJAH. The study will take place in the division of cardiology at the CMJAH, a academic state-owned tertiary PCI-capable healthcare facility in Johannesburg, South Africa. Participants will be followed over one year, and clinical outcomes will be measured at 30 days, three months, six months and one year from the index date of hospital discharge. The first day after hospitalisation will be considered day one of the follow-up.

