**Methods:**

This is a single-centre observational prospective cohort of all consecutive individuals presenting with an acute STEMI to the Charlotte Maxeke Johannesburg Academic Hospital (CMJAH) in Johannesburg, South Africa. Research data will be sourced on admission through electronic medical records, blood laboratory results and coronary angiography reports, and at follow-up through periodic telephonic interviews and standardised echocardiograms. At least 355 eligible participants will be continuously followed over one year, and clinical outcomes will be measured 30 days, three months, six months and one year after the index hospitalisation.

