## Methods

### Study aims

This study aims to determine the clinical outcomes of an acute STEMI within one year of clinical presentation to the division of cardiology at the CMJAH. The study also evaluates the association between baseline serum cardiac biomarkers of myocardial infarction and all-cause mortality within a year of acute STEMI.

The primary objective is:

To determine the all-cause mortality rate of an acute STEMI at 30 days, three and six months, and one year after the index presentation.

The secondary objectives include:

To determine the rates of cardiac-related re-hospitalisation, heart failure, angina, major bleeding, thromboembolism, non-fatal arrhythmias (namely, atrial fibrillation, ventricular tachycardia, and complete heart block) and planned or unplanned repeated revascularisation at 30 days, three and six months and one year after the index STEMI at CMJAH.To assess the relationship between all-cause mortality and the peak serum hs-cTnT, CRP and SUA measured on admission.To describe the baseline clinical characteristics of STEMI patients in our setting.To compare the clinical outcomes between STEMI patients who received thrombolysis, PCI, a pharmaco-invasive strategy and those who underwent no reperfusion at 30 days, six and three months, and one year after the index STEMI.To determine the baseline clinical predictors of all-cause mortality at 30 days, three months, six months and one year after the initial STEMI.To describe the adjuvant medical care provided and medication compliance rates at 30 days, three months, six months and one year after the index discharge from the hospital.

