#### Characteristics of study participants

All consecutive patients presenting to CMJAH with an acute STEMI diagnosis will be invited to participate in the study as shown in the flow diagram provided in Appendix A.

Inclusion criteria include:

Age ≥ 18 years.All confirmed acute STEMI diagnoses as per the fourth universal definition of myocardial infarction, i.e., myocardial injury evidenced by a rise and/or fall of serum cardiac troponin levels with at least one value above the 99th percentile of the upper reference limit, in the presence of the following, ischaemic symptoms and new ischaemic ECG changes, i.e., persistent ST-segment elevation of at least 1 mm measured from the J-point in at least two contiguous leads, or new pathological Q-waves or a new-onset left bundle branch block.All confirmed STEMI receiving the various STEMI management, i.e., thrombolysis, PCI, pharmaco-invasive approach, and no reperfusion.Able to give written informed consent.The participant or participant’s next of kin is reachable by cellphone.

Exclusion criteria include:

ACS other than STEMI, i.e., NSTEMI and unstable angina.Unable to give consent.Unreachable by telephone call (participant or their next of kin).Incomplete medical records.

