### Data collection

Research data will be collected from 01 May 2021 to 30 October 2022. The Primary Investigator (PI) will use the Research Electronic Data Capture (REDCap) software as the primary data collection tool. At baseline, the PI will capture demographic, clinical, calculated TIMI and GRACE scores, laboratory test results, ECG, echocardiographic, coronary angiographic, revascularisation and discharge medication data shown in Appendix B. The PI will create and access a reference list of the study participants’ hospital numbers and specific study numbers. The PI will retrieve these from the relevant progress notes, National Health Laboratory Service (NHLS) lab track, electronic medical records, and coronary angiogram report database of the division of cardiology at CMJAH.

The PI will telephonically contact all participants or their designated family members to monitor general well-being, medication compliance, outpatient cardiac clinic visits and cardiac-related re-admissions. When re-admitted to CMJAH, the PI will access the relevant hospital records to ascertain whether our study’s outcomes of interest occurred. Participants will be deemed compliant with medication if they say so during the telephonic interviews. The telephonic interviews will follow a closed-ended structured questionnaire, as depicted in Appendix C. Each participant will receive a telephonic interview call at 30 days, three months, six months and twelve months after the index hospital discharge date. All participants will be given the PI’s phone number and business card and encouraged to save the number on their cellphones when they sign informed consent forms so that doctors from other hospitals can contact the PI for cardiac-related referrals to CMJAH.

The PI will obtain the peak values of serum hs-cTnI, serum CRP and SUA from routine blood tests drawn at baseline for all participants. Automated messages generated through REDCap will be sent to remind both the PI and the participants of their scheduled outpatient clinic visits a week before the visits.

An experienced research sonographer will perform standardised echocardiograms during the outpatient clinic visits three months and one year after the index discharge. The two cardiologists who supervise the study will verify all echocardiograms. Appendix D shows the left ventricular parameters and valve analysis that will be recorded.

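### The primary mortality endpoint has two incompatible time origins, presentation and discharge; if the discharge clock governs the analysis, in-hospital deaths fall outside the estimate

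*Protocol article*

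**What the plan says.** All references are to the protocol article.

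- **Study aims, primary objective:** "To determine the all-cause mortality rate of an acute STEMI at 30 days, three and six months, and one year after the index presentation". The general aim in the same section agrees, referring to "clinical outcomes of an acute STEMI within one year of clinical presentation to the division of cardiology at the CMJAH".
- **Study design and setting:** "clinical outcomes will be measured at 30 days, three months, six months and one year from the index date of hospital discharge". The next sentence fixes the start of the count: "The first day after hospitalisation will be considered day one of the follow-up".
- **Abstract, Methods:** "clinical outcomes will be measured 30 days, three months, six months and one year after the index hospitalisation". This could mean from admission or from the end of the stay.
- **Characteristics of study participants:** entry is at presentation: "All consecutive patients presenting to CMJAH with an acute STEMI diagnosis will be invited to participate in the study". Participants must be able to give written consent, and those who cannot are excluded.
- **Data collection:** calls are made "at 30 days, three months, six months and twelve months after the index hospital discharge date". This is a contact schedule and defines no analysis clock.
- **Statistical analysis:** Kaplan-Meier curves, log-rank tests and Cox models are planned, with no time origin stated.

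The article nowhere says how a death before discharge is counted or timed.

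**The concern.** The two origins are not loose synonyms. Within the list of objectives, mortality and the other clinical events are timed from presentation or from the STEMI, while adjuvant care and medication compliance alone are timed from discharge. The authors therefore use the terms for different things. The study design section then applies the discharge origin to clinical outcomes in general.

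The choice decides which deaths are counted. Under the discharge clock a participant who dies during the index admission never reaches day one. The early phase is also where reperfusion is expected to act; the Background itself credits fibrinolysis with preventing early deaths. If survival were analysed on that clock, the comparison of reperfusion strategies and the models for predictors and biomarkers would be conditioned on survival to discharge, an event that follows treatment.

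The planned comparison with other settings suffers too. It cannot be read until the study's own origin is fixed.

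**Working it through.** **Step 1: set the statements side by side.**

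| Section | Time zero | Does a death before discharge count? |
|---|---|---|
| Study aims | Presentation | Yes |
| Study design and setting | Discharge; day one is the day after hospitalisation | No follow-up time exists |
| Abstract | Index hospitalisation | Unclear |
| Data collection | Discharge, for calls only | Not addressed |
| Statistical analysis | None given | Not addressed |

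The first two rows cannot both define the primary endpoint. They differ in who is at risk and in the calendar day on which each time point falls.

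**Step 2: direction of the difference.** Let h be mortality before discharge among enrolled participants, and m the mortality among those discharged alive.

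- Presentation clock: h + (1-h)m
- Discharge clock: m
- Difference: h + (1-h)m - m = h(1-m), which is positive whenever h > 0 and m < 1.

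This ignores the small shift of the calendar window by the length of the hospital stay.

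**Step 3: illustrative size.** The article gives no figure for this difference to reproduce. The inputs are:

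- m = 6.7% at one year and 2.4% at 30 days: the South African registry figures in the Background, described there as outpatient mortality.
- h = 2%, 5% and 10%: an assumption, because the article gives no in-hospital mortality.
- n = 355: the minimum sample size, used only to turn rates into counts.

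One-year mortality from presentation:

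- h = 2%: 0.02 + 0.98 × 0.067 = 0.0857, or 8.6%
- h = 5%: 0.05 + 0.95 × 0.067 = 0.1137, or 11.4%
- h = 10%: 0.10 + 0.90 × 0.067 = 0.1603, or 16.0%

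The discharge clock shows 6.7% each time. The shortfall h(1-m) is 0.02 × 0.933 = 1.9, 0.05 × 0.933 = 4.7 and 0.10 × 0.933 = 9.3 percentage points.

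Deaths among 355 participants enrolled at presentation:

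| Assumed h | In hospital, 355h | After discharge, 355(1-h) × 0.067 | Total | Share lost on discharge clock |
|---|---|---|---|---|
| 2% | 7.1 | 23.3 | 30.4 | 23% |
| 5% | 17.8 | 22.6 | 40.3 | 44% |
| 10% | 35.5 | 21.4 | 56.9 | 62% |

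At 30 days, with m = 2.4%, the same formula gives 0.02 + 0.98 × 0.024 = 4.4%, 0.05 + 0.95 × 0.024 = 7.3% and 0.10 + 0.90 × 0.024 = 12.2%, against 2.4%. The relative effect is larger at the earlier time point.

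**The case against.** The strongest reply is that nothing in the article excludes in-hospital deaths. Patients enter at presentation, the objective runs from presentation, and baseline data come from hospital records, so such deaths may well be recorded and counted. The flow diagram and the data collection forms are in appendices that are not shown. This stands: the loss follows from the stated clock and is not a stated rule. A reader might infer that the study drops in-hospital deaths and that its mortality is therefore understated. The article supports this only if the discharge clock governs the analysis.

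A reader might also infer that these patients vanish from every Kaplan-Meier curve and Cox model. The statistical analysis section gives no origin for either, and that detail may sit in a fuller document. Nor does the call schedule show an error, since calls timed from discharge are compatible with mortality timed from presentation.

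The discharge clock could be deliberate, because the Background points to a gap in outpatient follow-up data. In that case the primary objective is wrongly worded, and the contradiction remains.

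Two points weaken the figures. Patients too ill to consent are excluded, so in-hospital mortality among participants is probably lower than among all who present, which makes the upper end of the assumed range less plausible. And the Background calls the 6.7% outpatient mortality once, but later calls it the crude one-year rate and compares it with an overall death rate of 10.4% from another centre, so its own time origin is uncertain.

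**Conclusion.** The contradiction is in the current text and is certain: the primary objective counts from presentation, and the study design section counts from discharge. It affects which deaths enter the primary estimate, so it must be resolved.

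The downward bias is conditional on the discharge clock being used for analysis. Given that, its direction follows by arithmetic for any in-hospital mortality above zero. Its size cannot be taken from the article: the shortfall of 1.9 to 9.3 percentage points at one year rests on an assumed in-hospital mortality of 2% to 10% and on reading 6.7% as purely post-discharge. Conditioning of the reperfusion comparison and the predictor models on survival to discharge depends on the same reading of the clock.

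It would also go too far to say that a presentation clock yields mortality for all who present with STEMI. The consent requirement keeps deaths before consent out of the cohort whichever origin is used.

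**What to change.** 1. In Study design and setting, define time zero for mortality as the index presentation, in line with the primary objective, and bring the abstract into line.
2. Count deaths during the index admission in the mortality estimates at all four time points.
3. Report survival after discharge as a secondary landmark analysis, labelled as such, for comparison with outpatient registry figures.
4. Leave the telephone schedule in Data collection timed from discharge.
5. State that deaths before consent are not captured and that the estimate applies to consenting patients. Where consent follows presentation, an enrolled participant cannot have died in between; treat that gap as delayed entry, or state it as a limitation.

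The cost is a few sentences of wording and slightly more analysis work. Admission dates and in-hospital vital status should be available from the hospital records that the study already uses. The reported mortality will be higher if any participant dies in hospital.

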#### Characteristics of study participants

All consecutive patients presenting to CMJAH with an acute STEMI diagnosis will be invited to participate in the study as shown in the flow diagram provided in Appendix A.

Inclusion criteria include:

Age ≥ 18 years.All confirmed acute STEMI diagnoses as per the fourth universal definition of myocardial infarction, i.e., myocardial injury evidenced by a rise and/or fall of serum cardiac troponin levels with at least one value above the 99th percentile of the upper reference limit, in the presence of the following, ischaemic symptoms and new ischaemic ECG changes, i.e., persistent ST-segment elevation of at least 1 mm measured from the J-point in at least two contiguous leads, or new pathological Q-waves or a new-onset left bundle branch block.All confirmed STEMI receiving the various STEMI management, i.e., thrombolysis, PCI, pharmaco-invasive approach, and no reperfusion.Able to give written informed consent.The participant or participant’s next of kin is reachable by cellphone.

Exclusion criteria include:

ACS other than STEMI, i.e., NSTEMI and unstable angina.Unable to give consent.Unreachable by telephone call (participant or their next of kin).Incomplete medical records.

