Data from the South African Registry of Acute Coronary Events multinational Survey of current management Strategies (ACCESS) reported that the thirty-day and one-year outpatient all-cause mortality rates in STEMI patients were 2.4% and 6.7%, respectively [6]. The French Registry on Acute ST-elevation Myocardial Infarction (FAST-MI) of 2008 reported that in patients treated with thrombolysis, the thirty-day mortality rate is 9.2% without PCI and 3.9% when rescue PCI is subsequently performed (p = 0.044) compared to 2.8% in those who undergo a pharmaco-invasive approach (p = 0.147) [7]. According to the FAST-MI of 2008, the crude one-year survival rate is 78.5% in patients without reperfusion, 93.6% for thrombolysis, and 91.8% for PPCI (p < 0.001 for overall comparison; p = 0.31 for thrombolysis vs PPCI). When compared to other regions in SSA, the crude one-year mortality rate of 6.7% reported in the South African ACCESS registry was lower than the overall death rate of 10.4% reported in a single national referral centre study conducted in the Intensive Care Unit of Abidjan Heart Institute, in Côte d’ Ivoire [8].

An age of ≥ 70 years, female gender and heart failure on admission are significant factors predictive of mortality at thirty days and one-year follow-up of STEMI, irrespective of myocardial revascularisation strategy [8]. Diabetes mellitus on admission and a history of stroke or transient ischaemic attack (TIA) are also associated with a higher risk of death at one year [6]. In SSA, delayed access to emergency medical services (EMS) and healthcare facilities with reperfusion therapy limits favourable outcomes in STEMI patients [9]. In a local prospective cohort study at a single tertiary centre involving 100 STEMI patients, Meel et al. reported that only 37% of eligible patients received fibrinolytic therapy [10]. Only 3% received the medication within one hour. The median total time delay to administering a fibrinolytic agent was 270 min (45–584), with patient and transport delays being the most crucial reasons. For fibrinolytic therapy not given within one hour of hospital arrival, the calculated number of lives lost due to these delays was 32 patients per 1000 treated.

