Treatment guidelines recommend measuring serum CRP to aid in diagnosing and treating STEMI patients. STEMI patients with serum CRP > 3.0 mg/dL at or after discharge have a significantly higher risk of re-infarction, ischaemic stroke, coronary artery occlusion and death within two years of the index AMI [15]. The risk of mortality increases with higher CRP values at admission (Odds Ratio 1.04, 95% CI 0.91–1.20, p < 0.0001) and 30 days (Odds Ratio 1.12, 95% CI 0.93–1.34, p = 0.007) after hospital discharge [16].

In a systematic review and meta-analysis involving nine studies, Trkulja et al. showed that ‘high’ baseline SUA independently predicts all-cause mortality, re-infarction, angina, revascularisation and cardiac arrest at 30 days (Odds Ratio 2.26, 95% CI 1.85–2.77, p < 0.001), and at both 6 and 12 months (Hazard Ratio 1.30, 95% CI 1.01–1.68, p = 0.042) [17]. ‘High’ SUA refers to values in the hyperurecaemic, i.e., > 0.42 mmol/L and > 0.36 mmol/L or high-normal range, i.e., 0.31 mmol/L-0.42 mmol/L and 0.25 mmol/L -0.36 mmol/L in men and women, respectively. However, this study provided no data on the association between serial measurements of SUA at 30 days, six months and one year after hospital discharge and clinical outcomes in STEMI patients. Moreover, the combination of these three serum cardiac biomarkers might have an incremental value in the risk stratification of these patients.

Primary percutaneous coronary intervention (PPCI) is emergent PCI without prior fibrinolysis. It is the current reperfusion strategy of choice in STEMI patients who present within 12 h of symptom onset, provided it is conducted expeditiously within 120 min from the time of STEMI diagnosis [4]. A study by Zhu et al. showed that PPCI significantly reduces mortality, non-fatal re-infarction, and stroke by approximately 50% at 6 to 12 months (Odds Ratio 0.52, 95% CI 0.44–0.62, p < 0.001) [18].

However, fibrinolysis remains an important alternative reperfusion strategy that prevents early mortality in 30 per 1000 patients treated within 6 h after symptom onset. Fibrinolytic therapy should be administered within 12 h of symptom onset, provided that early primary PCI cannot be performed and there are no contraindications [19].

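### The crude log-rank comparison of reperfusion groups cannot separate late arrival from lack of treatment in the no-reperfusion group

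*Protocol article*

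**What the plan says.** All references are to the protocol article.

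- **Design** (Study design and setting): an "observational, prospective cohort of all consecutive individuals with an acute STEMI diagnosis".
- **Entry** (Characteristics of study participants): "All confirmed STEMI receiving the various STEMI management, i.e., thrombolysis, PCI, pharmaco-invasive approach, and no reperfusion". Neither the inclusion nor the exclusion list limits time from symptom onset.
- **Primary objective** (Study aims): "To determine the all-cause mortality rate of an acute STEMI at 30 days, three and six months, and one year after the index presentation". This is descriptive and covers the whole cohort.
- **Secondary objective** (Study aims): "To compare the clinical outcomes between STEMI patients who received thrombolysis, PCI, a pharmaco-invasive strategy and those who underwent no reperfusion".
- **Analysis** (Statistical analysis): one-year survival in the reperfusion groups is estimated by Kaplan-Meier without adjustment and compared by log-rank. Multivariable Cox regression is mentioned only for finding baseline clinical predictors of death.
- **Timing** (Background): "Fibrinolytic therapy should be administered within 12 h of symptom onset", and primary PCI is described as the "reperfusion strategy of choice in STEMI patients who present within 12 h of symptom onset".
- **Setting** (Background): delayed access to emergency services and to reperfusion is said to limit good outcomes. In a local cohort of 100 patients, "only 37% of eligible patients received fibrinolytic therapy".

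**The concern.** Two kinds of patient can end up in the no-reperfusion group. Some arrive after the 12 h that the Background cites and so, on that guidance, would seldom receive fibrinolysis or primary PCI. Others arrive in time and are not treated, and the local 37% figure leads one to expect such patients. The two are likely to differ in prognosis for reasons unrelated to treatment, because the article itself names delay as a determinant of outcome. An unadjusted log-rank test then compares groups that arrival time helps to define.

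The Discussion paragraph of the Abstract says that comparing outcomes between reperfusion strategies may guide clinicians where PCI access is limited. That use needs a contrast between patients who could have received either option. The limitations paragraph of the Discussion concedes unmeasured confounding in general terms, but time from onset can be measured, so the caveat does not cover it.

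**Working it through.** The plan states no figure that bears on this point, so there is none to reproduce. The check has two parts.

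**1. The sections side by side**

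| Question | What the article gives |
|---|---|
| Can late presenters enter? | Yes; no onset limit in the entry criteria |
| Which group can they enter? | No reperfusion, and also PCI, which the objective lists without a time limit |
| Can untreated patients within 12 h enter? | Yes; the same no-reperfusion group |
| Is delay prognostic? | Yes, according to the Background |
| Does the stated comparison account for delay? | No; unadjusted Kaplan-Meier and log-rank |

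These steps suffice to show that a crude difference has more than one explanation. They give no size.

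**2. An illustration with no treatment effect at all**

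Inputs:
- One-year mortality in patients within the window, p = 100% − 93.6% = 6.4%. The 93.6% is the survival under thrombolysis in the French registry cited in the Background, borrowed here for patients within the window, treated or not.
- N = 355, from Study sample size calculation. A 25% or 50% untreated share is assumed.
- Share s of late presenters within the no-reperfusion group: assumed.
- Ratio r of late to in-window mortality: assumed.
- All treated patients are pooled and taken to be within the window, for simplicity.

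Expected mortality in the no-reperfusion group is p × [1 + s(r − 1)], so the crude risk ratio is 1 + s(r − 1).

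| s | r | Mortality, no reperfusion | Crude risk ratio | Rejection in that direction |
|---|---|---|---|---|
| 0.25 | 1.5 | 6.4 × 1.125 = 7.2% | 1.12 | about 5% |
| 0.50 | 2 | 6.4 × 1.5 = 9.6% | 1.5 | 19% to 20% |
| 0.75 | 3 | 6.4 × 2.5 = 16.0% | 2.5 | 75% to 82% |

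The nominal rejection rate in one direction is 2.5%, taking the 0.05 level as two-sided. Rejection is Φ[(d − 1.96·se0)/se1], where d is the difference in proportions and se0 and se1 are its pooled and unpooled standard errors. For the middle row with half untreated (177.5 per group):
- d = 0.096 − 0.064 = 0.032
- se0 = √(0.08 × 0.92 × 2/177.5) = 0.0288
- se1 = √[(0.096 × 0.904 + 0.064 × 0.936)/177.5] = 0.0287
- Φ[(0.032 − 0.0564)/0.0287] = Φ(−0.85) = 0.198

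This is a comparison of two proportions standing in for the log-rank test, without censoring.

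The sign depends on r. If late presenters who reach enrolment do better, say 5% against 8% (both assumed, r = 0.625), then s = 0.5 gives 1 + 0.5 × (−0.375) = 0.81, and no reperfusion looks protective.

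**The case against.** The strongest reply is that nothing is wrong with entry. A consecutive all-comers cohort is what a descriptive mortality objective needs, and excluding late presenters would remove part of the population to be described. That stands, and the point is not aimed at eligibility.

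Other parts of the reply also stand:

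- **The 12 h figure is background guidance.** It is not a rule the study sets for itself, so the plan does not break its own limit.
- **The PCI group has no time limit.** A reader might infer that late presenters have no treated counterparts and that adjustment is useless. The group definitions do not support that, since late presenters may appear in the PCI group. It also means that mixing by arrival time is not confined to the untreated.
- **Late arrival is not shown to be common.** The Background's delay to fibrinolysis (median 270 min, 45 to 584) describes treated patients, and 584 min is 9.7 h, still below 12 h. The 37% concerns eligible patients. No section gives the share arriving after 12 h.
- **The direction is open.** Study design and setting counts follow-up from discharge, which would leave deaths in the first hours out of every group. Study aims counts from presentation. An argument from early survival therefore depends on which clock is used.
- **Unseen material.** Appendix B and any analysis plan are not shown and may include onset time or adjustment. TIMI and GRACE scores are captured at baseline.

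The reply does not remove the stated method. The article names an unadjusted comparison for the reperfusion groups and links the strategy comparison to clinical guidance.

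**Conclusion.** The point holds for the secondary strategy comparison and does not touch the primary objective. As planned, a crude difference between no reperfusion and the treated groups cannot be read as the effect of lack of treatment, because arrival time helps to determine group membership and is, on the article's own account, prognostic.

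Neither size nor direction can be derived from the documents. The illustrated risk ratios, from 0.81 to 2.5, rest on assumed late shares and mortality ratios. They show only that the distortion could be trivial or large.

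A reader might go further and infer that the entry criteria are faulty, or that any observed gap would be wholly due to late arrival. The documents support neither. The criteria fit the primary objective, and the whole-gap reading is only one possibility among several. The change is worth making because it is cheap and alters neither enrolment nor care.

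**What to change.** Leave enrolment and the overall mortality rate as they are. Amend the strategy objective in Study aims and the matching text in Statistical analysis as follows:

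1. Run the comparison of thrombolysis, PCI, pharmaco-invasive strategy and no reperfusion among participants presenting within 12 h of symptom onset. The 12 h serves here only to define an analysis set.
2. Report later presenters, treated or not, as a separate descriptive group.
3. Within the window, adjust for time from onset and baseline risk, for example with the TIMI or GRACE score already captured.
4. Describe any remaining difference as associational. The window does not remove confounding by indication, since patients who arrive in time and go untreated may differ in other ways.

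**Cost.** Fewer patients enter the comparison, from a cohort planned at 355, so its precision falls. Onset time must be taken from the admission record if Appendix B does not already include it.

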This study has several potential limitations. First, it is a single-centre study and thus prone to selection bias. Second, its observational nature may not allow us to control for unmeasured confounders that may contribute to the clinical outcomes observed. Third, although participants’ and participants’ next of kin’s cellphone numbers will be recorded, the prospective nature of the study makes it susceptible to loss to follow-up. Fourth, the follow-ups will be conducted through structured telephonic interviews, which may lead to patients omitting vital health data and, thus, under-reporting adverse cardiovascular events of interest to this study. Finally, the study site’s emergency department was not fully functional due to a fire incident that occurred prior to the start of the study, which may limit the number of participants presenting at our facility.

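### Excluding patients who cannot consent or have incomplete records conflicts with an all-consecutive mortality cohort and probably biases the death rate downward by an unknown amount

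*Protocol article*

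**What the plan says.** *Study design and setting* describes a "prospective cohort of all consecutive individuals with an acute STEMI diagnosis presenting to the CMJAH". *Characteristics of study participants* repeats the frame: "All consecutive patients presenting to CMJAH with an acute STEMI diagnosis will be invited to participate in the study". *Study aims* words the primary objective as follows: "To determine the all-cause mortality rate of an acute STEMI at 30 days, three and six months, and one year after the index presentation".

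Eligibility then narrows this frame. One inclusion criterion is "Able to give written informed consent", and the exclusions, after other forms of acute coronary syndrome and inability to consent, are "Unreachable by telephone call (participant or their next of kin).Incomplete medical records". The article describes no proxy, deferred or waived consent. It does not define an incomplete record, and it does not say when the telephone rule is applied. Reachability of the participant or next of kin also appears as an inclusion criterion.

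Among the limitations, the *Discussion* puts selection bias down to the single-centre design and says separately that "the prospective nature of the study makes it susceptible to loss to follow-up". It mentions neither the consent rule nor the records rule as a source of bias in the death rate.

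**The concern.** A mortality rate describes all consecutive presentations only if entry to the cohort does not depend on things that go with dying. Two of the rules probably do.

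- **Consent.** A patient who is in shock, ventilated or dies within hours cannot sign. The *Background* itself reports heart failure on admission as a predictor of death at 30 days and one year, so the sickest patients weigh heavily in this rate.
- **Incomplete records.** Completeness can be judged only after data have been collected. Applied as written, the rule can remove a patient whose death is already known, because some other item is missing.

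The rate will be set against those from high-income countries and other parts of sub-Saharan Africa, and the stated hypothesis is no significant difference from high-income countries. If local mortality is in fact higher, a downward bias moves the result towards that hypothesis. A larger sample does not reduce it.

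**Working it through.** The article states no figure for this bias, so there is none to reproduce. The calculation below only shows what size it could have.

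**Inputs from the article.** Observed one-year mortality is taken as m₁ = 6.7%, the South African registry rate quoted in the *Background*. The sample is n = 355 (*Study sample size calculation*).

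**Assumed inputs.** The share unable to consent is f = 5–10%, and their one-year mortality is m = 30–50%. The article gives neither. The assumed mortality is 4.5 to 7.5 times the observed rate (0.30/0.067 and 0.50/0.067).

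**Step 1: mortality among all presentations.** (1 − f)·m₁ + f·m

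| f | m | Calculation | All presentations | Shift from 6.7% |
|---|---|---|---|---|
| 5% | 30% | 0.95 × 0.067 + 0.05 × 0.30 | 7.9% | 1.2 points |
| 5% | 50% | 0.95 × 0.067 + 0.05 × 0.50 | 8.9% | 2.2 points |
| 10% | 30% | 0.90 × 0.067 + 0.10 × 0.30 | 9.0% | 2.3 points |
| 10% | 50% | 0.90 × 0.067 + 0.10 × 0.50 | 11.0% | 4.3 points |

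**Step 2: sampling error.** 1.96 × √(0.067 × 0.933 / 355) = 0.026, or 2.6 points. Only the last row exceeds it.

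**Step 3: when the bias exceeds sampling error.** The shift is f·(m − 0.067). It passes 0.026 when m > 0.067 + 0.026/f, that is above 33% at f = 10% and above 59% at f = 5%.

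**Step 4: milder assumptions.** Let RR be the ratio of mortality in excluded to enrolled patients, so that the shift is f·(RR − 1)·m₁. With f = 10% and RR = 2 it is 0.10 × 1 × 6.7 = 0.7 points. With f = 20% and RR = 3 it is 0.20 × 2 × 6.7 = 2.7 points. With RR = 1 it is zero.

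**Step 5: the records rule.** At 6.7%, 355 patients give about 24 deaths (355 × 0.067 = 23.8). Removing one known death changes 24/355 = 6.76% to 23/354 = 6.50%, about 0.26 points for each death removed.

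**Scale.** The *Background* remarks on the difference between 6.7% and 10.4% (Côte d'Ivoire), which is 3.7 points. The assumed range of 1.2–4.3 points extends past that difference.

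**The case against.** Several stronger readings are tempting, and the article does not support them.

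- **That the telephone rule drops participants who have died.** A reachable next of kin satisfies the rule, *Data collection* says designated family members may be called, and the exclusion mirrors an inclusion criterion. The natural reading is an enrolment check. The *Discussion* treats later non-contact as loss to follow-up, and the planned Kaplan-Meier and Cox analyses can censor it. What stands is that no time point is given.
- **That early deaths are incomplete by definition, for want of an angiogram or discharge medication.** *Data collection* lists what will be captured and does not tie the exclusion to that list. Patients without reperfusion, who may have no angiogram, are expressly eligible. What stands is that the term is undefined and can be applied after the outcome is known.
- **That the bias matches or exceeds sampling error.** One of the four consent scenarios exceeds 2.6 points. A telephone scenario with 10% unreachable at three times the mortality gives 0.9 × 6.7 + 0.1 × 20.1 = 8.0%, a shift of 1.3 points, half the sampling error.

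The clock also matters. *Study design and setting* measures outcomes from discharge. On that reading in-hospital deaths fall outside follow-up anyway, and a 30–50% mortality among patients unable to consent would largely not apply. The quoted 6.7% is itself called an outpatient rate. This weakens the size but does not remove the conflict, because the primary objective counts from presentation.

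Finally, the flow diagram (Appendix A) and data form (Appendix B) are not shown and may define completeness or record who was screened. They would not alter the exclusion printed in the article.

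**Conclusion.** The point holds for the consent and incomplete-records rules. Both are stated exclusions, both are plausibly linked to early death, and neither fits a cohort described as all-consecutive with mortality from presentation as its primary objective. The listed limitations do not cover them.

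The likely direction is downward. That is an inference, resting on excluded patients dying more often than enrolled ones, and the article does not document it. The size is unknown: 1.2–4.3 points under the assumed 5–10% non-consent with 30–50% mortality, against 2.6 points of sampling error, and less under milder assumptions or a clock that starts at discharge.

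A reader might infer that all the exclusions depend on the outcome, or that the bias is known to be larger than sampling error. Neither follows. Ability to consent and telephone access can be assessed at entry and may go with prognosis, but they are not defined by it. The telephone rule needs only a stated time point.

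**What to change.** 1. Delete incomplete medical records as an exclusion. Keep these patients in the mortality analysis and handle missing covariates as missing data, for example by multiple imputation.
2. State that the telephone criterion applies at enrolment only. Censor later losses at the last date known alive, and add a best-case and worst-case sensitivity analysis of one-year mortality.
3. Report the number of STEMI presentations not enrolled, by reason, with in-hospital vital status where ethics approval allows. If that cannot be done, restrict the stated estimand to consenting patients and drop the all-consecutive description.

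The cost is a change to the eligibility and analysis wording, some imputation work, a short count of presentations not enrolled, and possibly an ethics amendment for de-identified counts.
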